### Satiety hormones

At each of the five time points during the OGTT, additional blood samples will be collected for measurement of satiety hormones including insulin. Blood will be drawn into a cooled EDTA vacutainer tube containing diprotinin-A (0.034 mg/ml blood; MP Biomedicals, Irvine, CA); Sigma protease inhibitor (1 mg/ml blood; Sigma Aldrich, Oakville, ON, Canada) and Roche Pefabloc (1 mg/ml of blood; Roche, Mississauga, ON, Canada) [72]. Blood will be centrifuged within 30 min and plasma analyzed for ghrelin (active), insulin, leptin, glucose-dependent insulinotropic polypeptide (GIP) (total), GLP-1 (active), and PYY (total) concentrations using a Milliplex MAP Human Gut Hormone Panel Kit (Millipore, St Charles, MO). Surrogate markers of insulin resistance, HOMA and QUICKI, will be quantified as per our previous work [99].

### Mechanistic secondary outcomes

#### Gut Microbiota

Stool will be collected at baseline and follow-up for analysis of gut microbiota. Participants will be instructed on proper methods for stool collection and all materials will be provided in a convenient specimen collection kit. Each subject will collect 2 tablespoons of stool into a pre-labeled sterile container. The container will be sealed, placed in a biohazard bag, and immediately stored in a standard home freezer (−20 °C). The specimen will be transported to our research lab within 4 days of collection in a Styrofoam container on an ice pack and transferred to −80 °C for longer term storage. For analysis of fecal microbiota, total DNA will be extracted from 150 mg of stool using the Qiagen QIAamp™ DNA Stool Mini Kit. Uniform bacterial DNA extraction is ensured by the addition of a 2-minute mechanical bead (0.1 mm zirconia:silica) beating step following addition of buffer ASL to the samples. DNA quantity and purity will be measured using a nanoscale spectrophotometer. To understand the functional and metabolic capabilities of the gut microbiota [100] and how prebiotics impact the metabolic capacity of the entire microbiome, whole genome shot-gun sequencing will be performed to analyze both the microbial composition and potential metabolic functions at the University of Alberta’s Applied Genomic Center. Fecal DNA will be used as input for the Illumina Nextera® XT DNA Sample Preparation Kit to construct indexed paired-end DNA libraries as previously described [101]. A final constructed paired-end indexed library set will be run on a Bioanalyzer 2100 using Agilent High Sensitivity DNA Kit to acquire library average size distribution (Agilent Technologies, Santa Clara). Final libraries will be quantified using a Qubit® 1.0 fluorometer and the Qubit® dsDNA HS assay (Life Technologies, Carlsbad). Obtained quantification and average size distribution of the final Nextera® XT libraries will be used to calculate molarity of the library according to the Nextera® Library Validation and Cluster Density Optimization Technical Note. Libraries are normalized to 2nM and pooled together using equal volume aliquots. The pooled and indexed library set is denatured, diluted, and sequenced on an Illumina MiSeq. Sequencing parameters consist of: paired-end 251 bp dual index sequencing chemistry using MiSeq Reagent Kit-v2 (500 cycle) and FASTQ Only workflow. Produced FASTQ files are then subjected to bioinformatics analysis. The raw FASTQ files are first filtered for adapter sequences and end trimmed of bases with quality less than 15. Read ends are then aligned against a set of mitochondrial databases with SOAPalign, with unaligned reads passed to each successive alignment. Read ends unaligned to mitochondrial databases are aligned to human, bacterial, and viral databases generated from NT, using SOAPalign. SpecI (http://vm-lux.embl.de/~kultima/MOCAT/) will be used to determine species composition and HUMAnN (http://huttenhower.sph.harvard.edu/humann) used for the characterization of microbial pathways in the communities.

### Endotoxin

Serum endotoxin will be measured using a PyroGene recombinant factor C endotoxin detection kit (Lonza, Walkersville, MD) as per our previous work [75].

### Volatile organic compounds

Functional capabilities of microbiota will be assessed in terms of bacterial production of VOC. At the time of analysis, fecal samples will be thawed and a carboxen/polydimethyl-siloxane solid phase micro-extraction (SPME) fiber will be placed into the sample collection vial by injecting it through the septum in the cap. The SPME fiber will be left in the vial headspace for 20 minutes to fully absorb the VOC. The fiber will then be retracted into the needle and transferred to the injector port for gas chromatographic (GC) analysis. Two GC machines connected in serial are used to resolve VOC that are detected by mass spectrometry (MS). Compounds are then identified by reference to the NIST 08 MS library.

### *De Novo* lipogenesis

Energy reduction and weight loss significantly reduces lipogenesis, contributing to reduction in steatosis [102–106]. As part of our mechanistic investigation, fatty acid synthesis will be measured from fasting plasma samples using the deuterium incorporation method as per established methods [12, 107]. This protocol will be performed at a baseline visit prior to the OGTT (Fig. 1). Briefly, deuterium-labeled water (^2^H_2_O; 99.9 atom %; Cambridge Isotope Laboratories, Inc.; Tewksbury, MA) will be provided to participants at a dose of 1 g/kg body water (estimated as 60 % of body weight) to ingest [107]. On day 1, a fasting blood sample will be taken to measure background ^2^H enrichment, and on day 6, participants will ingest a single dose of ^2^H_2_O, as well as be provided with a second dose diluted in 1.5 L of water to consume at regular intervals over the next 24 h [107]. On day 7 at the inpatient visit, a fasting blood sample will be taken for measurement of ^2^H incorporation into triglyceride (TG) and plasma water. Plasma will be ultracentrifugated to isolate total TG-rich lipoproteins, which at fasting will be primarily VLDL arising from the liver [12, 108]. Samples will be stored at −80 °C until further analysis. Folch extraction and thin layer chromatography will be used to isolate the TG portion, which will be saponified and methylated to prepare fatty acid methyl esters (FAME) for GC/P/IRMS analysis [107]. Samples will be analyzed for ^2^H enrichment in major lipogenic fatty acids (14:0, 16:0, 16:1, 18:0, and 18:1). Proportion of newly-synthesized fatty acid will be calculated for each fatty acid using established equations [107].

### Sample size calculation

Our sample size is based on the primary outcomes of hepatic injury and liver fat. For hepatic injury, we used pilot data from our lab to determine that a sample size of *n* = 19 in each group would have 80 % power to detect a difference in liver stiffness of 4.1 kPa with FibroScan assuming a standard deviation of 4.0 kPa and a 0.025 two-sided significance level. For the Fibrotest [109], a sample size of *n* = 10 per group would have 80 % power to detect a difference in Fibrotest score (0.0 to 1.0) of 0.08 assuming a standard deviation of 0.056 and a 0.025 two-sided significance level. For liver fat measured by MRI [110], a sample size of *n* = 25 per group will have 80 % power to detect a difference in hepatic fat of 4.4 % assuming a standard deviation of 5.0 % and a 0.025 two-sided significance level. Based on these calculations, we will enroll *n* = 25 per group. Assuming a dropout rate similar to that in our previous prebiotic trial [72] of approximately 20 %, we will recruit a total of 60 participants (*n* = 30 per group).

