### Statistical analyses

Statistical analyses will be performed using SPSS 22.0 software (IBM, Armonk, NY). Values with skewed distribution will be logarithmically transformed prior to analysis. Baseline characteristics will be compared between groups using chi-square for categorical variables and t-tests for continuous variables. Primary analysis will be performed on an intent-to-treat basis, regardless of subject compliance. The primary outcome measures are change from baseline to 24 weeks in hepatic injury (Fibrotest, FibroScan) and liver fat (percent measured by MRI). ANCOVA, with testing for confounding factors (sex) and potential covariates (BMI, age and fasting insulin) will be used to assess the difference between groups at weeks 0 and 24. Should the main effect of diet be significant, Tukey’s multiple comparison test will be used. Secondary outcomes measured at 0 to 24 weeks (e.g. satiety hormones, body fat, glycemia and insulinemia) will be analyzed with ANCOVA as above. For variables measured over time (e.g. body weight, satiety hormones and glucose at 0, 30, 60, 120 and 180 minutes), a mixed model of repeated measures ANCOVA will be applied to examine the effect of treatment, time and their interaction. Our planned secondary analysis will be per protocol with all participants who complete the 24 week intervention and are compliant based on consumption of ≥80 % the product doses. Cases with missing outcome data will be excluded from analysis. Results will be considered statistically significant (2-sided) at *P* ≤ 0.025 (Bonferroni adjustment for 2 primary outcomes).

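### Allowing for 20% dropout by multiplying 25 by 1.2 leaves 24 evaluable per group, so power for MRI liver fat is about 79% by the protocol's own formula, not 80% (a minor error)

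*Protocol article*

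**What the plan says.** The protocol article's section "Sample size calculation" gives three requirements per group at 80% power and two-sided 0.025: 19 for FibroScan, 10 for Fibrotest and 25 for MRI liver fat. The last reads "For liver fat measured by MRI [110], a sample size of *n* = 25 per group will have 80 % power", for a "difference in hepatic fat of 4.4 % assuming a standard deviation of 5.0 % and a 0.025 two-sided significance level". The largest figure becomes the target: "Based on these calculations, we will enroll *n* = 25 per group".

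The allowance for losses follows. "Assuming a dropout rate similar to that in our previous prebiotic trial [72] of approximately 20" %, the protocol says, "we will recruit a total of 60 participants", which is 30 per group.

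The section "Statistical analyses" settles what happens to participants without a week-24 scan: "Cases with missing outcome data will be excluded from analysis".

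**The concern.** The sample size section treats 25 per group as the number needed and 30 as the number that protects it against a 20% loss. These do not agree, because 20% of 30 is 6, which leaves 24. MRI liver fat sets the trial size and has almost no reserve, so it is the outcome that falls below its stated power. MRI is done only at baseline and week 24 (section "Primary outcome"), and cases with missing outcomes are excluded. A participant who leaves without the second scan therefore contributes nothing to this comparison.

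What is at stake is the accuracy of a stated power on a primary outcome. The validity of the analysis is not in question.

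**Working it through.** **Inputs, all from "Sample size calculation".** MRI difference 4.4 points, SD 5.0, two-sided alpha 0.025, power 80%, target 25 per group, dropout about 20%, 30 recruited per group. Groups are of equal size (section "Randomization").

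**1. Reproduce the protocol's figures.** Normal approximation for two means:

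n per group = 2 × [(z₁ + z₂) × SD / difference]², with z₁ = 2.2414 (two-sided 0.025) and z₂ = 0.8416 (80% power), which sum to 3.083.

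- MRI: 2 × (3.083 × 5.0/4.4)² = 24.5, so 25. Matches.
- FibroScan (4.1 kPa, SD 4.0): 2 × (3.083 × 4.0/4.1)² = 18.1, so 19. Matches.
- Fibrotest (0.08, SD 0.056): 2 × (3.083 × 0.056/0.08)² = 9.3, so 10. Matches.

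All three agree, so this is taken as the protocol's formula. The t-based (noncentral t) calculation for MRI needs 26.

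**2. Dropout allowance.**

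- Protocol's figure: 25 × 1.2 = 30.
- Number that leaves 25 after a 20% loss: 25/(1 − 0.20) = 31.25, so 32 per group, 64 in total.
- What 30 leaves: 30 × 0.80 = 24.
- Dropout at which 30 still leaves 25: 1 − 25/30 = 16.7%.

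**3. MRI power at the number left.** Normal approximation: power = Φ[difference/(SD × √(2/n)) − 2.2414].

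At n = 24: 4.4/(5.0 × √(2/24)) = 3.048, and Φ(3.048 − 2.241) = Φ(0.807) = 79.0%.

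| Evaluable per group | Normal approximation | t-test (noncentral t) |
|---|---|---|
| 24 | 79.0% | 76.5% |
| 25 | 80.8% | 78.5% |
| 26 | 82.4% | 80.3% |

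**4. Difference detectable with 80% power at 24 per group.** Normal approximation: 3.083 × 5.0 × √(2/24) = 4.45 points. By the t-test it is 4.58, about 4.6.

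**5. Where the t-test shortfall comes from.** The gap between 80% and 76.5% is 3.5 points. Of this, 80 − 78.5 = 1.5 points would be there at the full 25 per group and come only from using the t distribution. The dropout allowance accounts for the remainder, about 1.9 points before rounding.

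**6. The other two measures at 24 per group.** FibroScan: about 90% (normal approximation) or 89% (t-test). Fibrotest: over 99% by either.

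**The case against.** The best defence concerns size. By the protocol's own formula the loss is one participant per group and 1.8 points of power, which ends 1.0 point under 80%. The dropout rate is given only as approximate and is borrowed from an earlier trial; five losses out of 30 would leave exactly 25. The normal approximation is a standard planning formula, so the t-based 76.5% should not be charged wholly to the dropout step. All of this stands, and it makes the point minor. It does not make the stated figures consistent: at the 20% the protocol itself names, 24 remain, and power is below 80% by either method.

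Three further readings are tempting, and the document does not support them.

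- A reader might infer that the trial is materially underpowered, or that 76.5% is the effect of the dropout error. It is not: about 1.5 of those 3.5 points come from the change of formula.
- A reader might lower the power further by applying a stricter alpha because three measures are called primary. That is a separate multiplicity question. Both sections use 0.025 consistently, and it has no bearing on the dropout arithmetic.
- A reader might dismiss the shortfall because the planned ANCOVA will recover the power. The listed adjustment factors are sex, BMI, age and fasting insulin. Baseline liver fat is not named, the sample size section does not say whether 5.0 is the SD of change, and no correlation is given. The gain may be real but cannot be counted from what is written.

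**Conclusion.** The point holds as a minor arithmetic error. The dropout allowance was multiplied on instead of divided out, so 30 per group leaves 24 rather than 25 at 20% dropout. MRI liver fat then has about 79% power for 4.4 points by the protocol's formula (76.5% by the t-test) instead of 80%.

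This rests on dropout of exactly 20% in each group, on every dropout lacking the week-24 MRI, and on an unadjusted two-group comparison with SD 5.0, which is how the protocol computed its own figure. FibroScan and Fibrotest are not affected. No analysis or decision rule changes.

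**What to change.** Keep 60 and correct the statement. Suggested wording: *With 30 recruited per group and 20% dropout, about 24 per group are expected to be evaluable. This gives about 79% power (normal approximation; about 77% by t-test) to detect a 4.4-point difference in liver fat, assuming SD 5.0 and two-sided alpha 0.025. The difference detectable with 80% power is 4.45 points (4.6 by t-test).*

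This costs one sentence and a slightly less favourable figure, with no extra participants. If the team prefers to protect the target of 25 instead, the consistent number is 32 per group (64 in total), four more participants than planned.

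Any credit for ANCOVA should be claimed only if baseline liver fat is explicitly added as a covariate and 5.0 is confirmed to be the SD of change, with the assumed correlation stated.

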### Statistical analyses

Statistical analyses will be performed using SPSS 22.0 software (IBM, Armonk, NY). Values with skewed distribution will be logarithmically transformed prior to analysis. Baseline characteristics will be compared between groups using chi-square for categorical variables and t-tests for continuous variables. Primary analysis will be performed on an intent-to-treat basis, regardless of subject compliance. The primary outcome measures are change from baseline to 24 weeks in hepatic injury (Fibrotest, FibroScan) and liver fat (percent measured by MRI). ANCOVA, with testing for confounding factors (sex) and potential covariates (BMI, age and fasting insulin) will be used to assess the difference between groups at weeks 0 and 24. Should the main effect of diet be significant, Tukey’s multiple comparison test will be used. Secondary outcomes measured at 0 to 24 weeks (e.g. satiety hormones, body fat, glycemia and insulinemia) will be analyzed with ANCOVA as above. For variables measured over time (e.g. body weight, satiety hormones and glucose at 0, 30, 60, 120 and 180 minutes), a mixed model of repeated measures ANCOVA will be applied to examine the effect of treatment, time and their interaction. Our planned secondary analysis will be per protocol with all participants who complete the 24 week intervention and are compliant based on consumption of ≥80 % the product doses. Cases with missing outcome data will be excluded from analysis. Results will be considered statistically significant (2-sided) at *P* ≤ 0.025 (Bonferroni adjustment for 2 primary outcomes).

Shotgun sequencing and GC-MS produce large datasets profiling microbiota composition and function and VOC metabolites, respectively. Binary as well as abundance data will be used in modeling VOC data. OPL-S coefficients determine the major variables contributing to discrimination in the model. VOC of interest will be identified with 90 % probability by referencing to mass spectral library standards of the National Institute of Standards and Technology (NIST08) database. Bacterial communities will be quantitatively assessed by Bray-Curtis dissimilarity matrix and Shannon-Wiener diversity index. Relative abundance data will be transformed [log(X + 1)] prior to generation of the resemblance matrix. To reduce dimension of explanatory variables and identify bacteria that were potentially acting in groups we will conduct hierarchical clustering analysis using Spearman rank correlation with complete linkage and groups identified based on correlations >0.5. Distinct bacteria tax identified from hierarchical clustering analysis will be compared across groups and time-points using formal parametric/non-parametric statistical methods such as the Dirichlet-multinomial distribution test, Mantel test, NP-Manova etc. We will analyze the prebiotic and placebo participants in terms of fecal microbiota, VOC, lipogenesis, clinical data, and host metabolic, nutritional, and inflammatory parameters using differential correlation analysis. Features will be compared using a Spearman’s rank order correlation coefficient and correlations above a defined threshold will be compared between groups. We will then graph the correlations that are statistically different between the groups to identify the pairs of features (i.e. the different VOC metabolites and bacteria between treatments) that distinguish the responses. The network models will be visualized in the popular open-source Cytoscape software.

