### Randomization

Participants will be randomized in equal numbers to two groups, stratified by sex, BMI, and age for allocation into prebiotic or placebo arms. Randomization sequences will be prepared by an independent statistician and entered into a web-based central randomization program. Sequences will not be revealed to investigators or study staff. Randomization will be in blocks of 4 within each sex/age/BMI stratum. To maintain blinding of the trial coordinator and registered dietitian, a research assistant with no involvement in the study will use the central randomization program at the randomization visit. Study personnel will be unaware of treatment allocation prior to the assignment of interventions, using sequentially numbered, opaque, sealed envelopes to maintain allocation concealment. The clinical trial coordinator will enroll participants. Participants, research staff and outcome assessors will be blinded to participants’ assigned group. Participants will receive the prebiotic or placebo supplement in identical foil packets to maintain blinding. An overview of the study design and measurement outcomes is presented in Fig. 1.

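### The primary ANCOVA does not commit to the stratification factors: sex is to be tested, and BMI and age are only potential covariates, so the gain from stratifying may be lost

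*Protocol article*

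**What the plan says.** Under Randomization, the protocol article states that participants are "stratified by sex, BMI, and age for allocation into prebiotic or placebo arms". It adds: "Randomization will be in blocks of 4 within each sex/age/BMI stratum". Allocation is 1:1.

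Under Statistical analyses, the primary comparison is "ANCOVA, with testing for confounding factors (sex) and potential covariates (BMI, age and fasting insulin". No test, threshold, retention rule or final covariate list follows, and nothing elsewhere in the article says that the three stratification factors enter the model regardless. The same section plans baseline significance tests: "Baseline characteristics will be compared between groups using chi-square for categorical variables and t-tests for continuous variables". It does not link those tests to the choice of covariates. The significance level is 0.025 two-sided, described as "Bonferroni adjustment for 2 primary outcomes".

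**The concern.** Stratified allocation makes the arms more alike on sex, BMI and age than simple randomisation would. The estimated treatment difference then varies less from trial to trial. A model that omits the factors does not see this: it leaves their variance in the residual, so its standard error is too large. The test then rejects less often than its nominal level under the null, and it forgoes power under the alternative. The design supplies precision and the analysis discards it.

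The natural reading of the sentence is that the data decide whether sex, BMI and age are kept. Treating sex as a confounder to be tested for does not suit this design either. Randomisation rules out systematic confounding by sex, and stratifying by sex limits chance imbalance as well. A check of baseline balance would therefore seldom retain these factors, even when they predict the outcome well.

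**Working it through.** **1. The plan's own sample sizes.** Inputs from Sample size calculation: two-sided level 0.025, power 80 %, and for MRI a "difference in hepatic fat of 4.4 % assuming a standard deviation of 5.0 % and a 0.025 two-sided significance level".

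n per group = 2 (z₀.₉₈₇₅ + z₀.₈₀)² (SD/difference)², with 2 × (2.2414 + 0.8416)² = 19.01.

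- FibroScan: 19.01 × (4.0/4.1)² = 18.09, so 19.
- FibroTest: 19.01 × (0.056/0.08)² = 9.31, so 10.
- MRI liver fat: 19.01 × (5.0/4.4)² = 24.55, so 25.

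All three stated figures are reproduced (the noncentral t gives 20, 11 and 26). They take no credit for covariates.

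**2. Direction and limit, by formula.** If the arms were perfectly balanced on factors explaining a share R² of outcome variance, the unadjusted test statistic would have standard deviation √(1 − R²) under the null instead of 1. In large samples its size would be 2[1 − Φ(2.2414/√(1 − R²))]:

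- R² = 0.15: 2.2414/0.922 = 2.431, size 0.015.
- R² = 0.30: 2.2414/0.837 = 2.679, size 0.007.

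Real balance is looser, because BMI and age are balanced only by category, blocks are left incomplete and some participants drop out. The true figures should therefore lie between these and 0.025.

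**3. Simulation.** Taken from the article: 60 randomised 1:1, permuted blocks of 4 within strata, SD 5.0, difference 4.4, level 0.025, and 50 analysed (25 per group). Assumed, because the article gives neither: eight strata (sex, BMI and age each in two classes) and R² of 0, 0.15, 0.30 and 0.50, shared equally by the three factors. Also assumed: fasting insulin is unrelated to outcome, and losses are at random. There were 10,000 runs under the null (simulation error about ±0.003) and 4,000 under the alternative (about ±0.012).

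Type I error, nominal 0.025:

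| Rule | R² 0 | 0.15 | 0.30 | 0.50 |
|---|---|---|---|---|
| Factors left out | 0.023 | 0.018 | 0.012 | 0.008 |
| Kept if imbalanced at p<0.05 | 0.023 | 0.019 | 0.013 | 0.008 |
| Kept if related to outcome at p<0.05 | 0.025 | 0.028 | 0.025 | 0.026 |
| Sex, BMI, age always in | 0.025 | 0.027 | 0.023 | 0.025 |
| Any of the 16 covariate sets significant | 0.033 | 0.041 | 0.040 | 0.047 |

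Power for a difference of 4.4:

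| Rule | R² 0 | 0.15 | 0.30 | 0.50 |
|---|---|---|---|---|
| Factors left out | 0.78 | 0.79 | 0.80 | 0.81 |
| Kept if imbalanced at p<0.05 | 0.78 | 0.79 | 0.80 | 0.81 |
| Kept if related to outcome at p<0.05 | 0.79 | 0.83 | 0.90 | 0.97 |
| Sex, BMI, age always in | 0.77 | 0.84 | 0.91 | 0.97 |

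The 16 sets are 2⁴, each of the four named variables being in or out.

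**4. Reading the tables.** Leaving the factors out forgoes 0.84 − 0.79 = 5 points at R² 0.15 and 0.91 − 0.80 = 11 points at R² 0.30. A second simulation of the same design gave true sizes of 0.018 and 0.011, and power of 0.79 and 0.79 against 0.84 and 0.89 with the factors always in. The gaps there are 5 and 10 points. Retention on baseline imbalance behaves almost exactly like omission. Retention on association with outcome costs about one point. At R² = 0, always including the three factors costs about one point (0.784 against 0.770); a fourth uninformative covariate takes power to 0.759.

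The simulated models did not contain the baseline value of the outcome. R² here is therefore the share of variance in the analysed outcome, before any gain from that baseline.

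**The case against.** The strongest reply is that the sentence is ambiguous rather than wrong. It names four variables and gives no rule for dropping any of them. It could mean that all four are entered and their effects reported, and an analysis plan not shown here may settle the list. That stands in part: selection by test is the natural reading, not the only one. But the article does not merely leave the list open. It describes an approach that makes the stratification factors conditional, and a plan that fixed them would have to depart from it.

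Second, even with the factors omitted, power stays at about 78 to 81 %, close to the planned "80 % power to detect a difference in hepatic fat of 4.4" %. This is correct. What is forgone is a gain above plan, and only if the factors predict the outcome.

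Three stronger readings are tempting, and the article supports none of them.

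- **An inflated type I error.** The 0.033 to 0.047 in the tables requires picking the covariate set by the treatment p-value. Nothing in the article says this will be done, so the figure is a bound, not a forecast. Selection on association with outcome keeps the size at 0.025 to 0.028.
- **Adjustment for week-24 BMI or insulin.** The article proposes no such covariate. BMI is a randomisation factor and hence a pre-treatment value. The missing word baseline is a gap in wording, more open for insulin than for BMI.
- **Baseline tests that choose the model.** The article reports them as a comparison and does not tie them to the ANCOVA. Nor are they wholly without information here: cases with missing outcomes are excluded, so the analysed set need not keep the randomised balance.

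**Conclusion.** The point holds as a mismatch between design and analysis. The factors used to randomise are not guaranteed a place in the primary model. If they are omitted, or kept only on baseline imbalance, the test at 0.025 has a true size of about 0.018 at R² 0.15 and 0.011 to 0.013 at R² 0.30. It forgoes about 4 to 5 and 10 to 11 power points respectively, and nothing at R² = 0. If they are kept on association with outcome, almost nothing is lost.

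The direction follows from the design. The size rests on the assumed R², on eight strata and on a retention rule that the article does not state. The sample size of 25 evaluable per group is unaffected. This is a wording correction worth making because it is nearly free. It is not evidence that the planned error rate will be exceeded.

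**What to change.** Replace the covariate clause under Statistical analyses with a statement to this effect: for each primary measure, the ANCOVA contains treatment, the baseline value of that measure, sex, baseline BMI and age, irrespective of any test of balance or association. Say that baseline fasting insulin is either always included or left to a named sensitivity analysis, and write baseline before BMI and insulin. Drop the reference to testing sex as a confounder. If the baseline comparisons are kept, add that they play no part in choosing covariates.

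The cost is four degrees of freedom (baseline outcome, sex, BMI, age), or five with insulin, out of about 50 analysed. In the worst case simulated, where the factors explain nothing, the three stratification factors cost about one point of power. No new data, visits or participants are needed.

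### The primary ANCOVA leaves out each outcome's own baseline value and describes its contrast loosely, so precision is lost and the primary test is not uniquely stated

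*Protocol article*

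**What the plan says.** All of this stands in the article's Statistical analyses section unless noted.

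- Outcome: "The primary outcome measures are change from baseline to 24 weeks" in Fibrotest, FibroScan and MRI liver fat. The Primary outcome section agrees, and schedules these measures at baseline and 24 weeks.
- Model: "ANCOVA, with testing for confounding factors (sex) and potential covariates (BMI, age and fasting insulin" are the terms named. The baseline value of the outcome being analysed is not among them.
- Contrast: the model "will be used to assess the difference between groups at weeks 0 and 24".
- Follow-up step: "Should the main effect of diet be significant", Tukey's procedure is applied.
- Secondary outcomes measured at 0 and 24 weeks use the same ANCOVA. For variables measured over time, "a mixed model of repeated measures ANCOVA will be applied to examine the effect of treatment, time and their interaction"; the examples given there are not primary outcomes.
- The Randomization section stratifies by sex, BMI and age.

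**The concern.** The outcome definition and the described test do not quite match. Change to week 24 calls for one between-group contrast. The text instead speaks of group differences at two time points, one of which precedes treatment. A difference at week 0 in a randomised trial is chance and not an effect.

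The covariate list is explicit and includes one baseline laboratory value, fasting insulin. It leaves out the covariate that is usually most prognostic for a week-24 measurement: the same measurement at baseline. That value is already collected for all three primary measures. In a trial of 60 participants, discarding it gives away precision at no saving.

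The loose contrast also matters for pre-specification. A change-score comparison, a comparison of week-24 values and a comparison involving both visits can give different P values from the same data.

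**Working it through.** **1. The plan's own sample sizes.** The Sample size calculation section gives differences and SDs of 4.1 and 4.0 kPa (FibroScan), 0.08 and 0.056 (Fibrotest), and 4.4 and 5.0 (MRI), with 80% power and two-sided alpha 0.025. An unadjusted two-sample comparison by the normal approximation is

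n per group = 2 (z₀.₉₈₇₅ + z₀.₈₀)² (SD/difference)² = 2 × (2.241 + 0.842)² × (SD/difference)²

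- FibroScan: 18.1, so 19
- Fibrotest: 9.3, so 10
- MRI: 24.5, so 25

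All three stated figures reproduce. The planned power therefore took no credit for a baseline covariate.

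**2. Inputs for the comparison.** MRI sets the sample size and is used here: "80 % power to detect a difference in hepatic fat of 4.4" percentage points, SD 5.0, alpha 0.025. With 30 recruited per arm and 20% dropout, 30 × 0.8 = 24 per arm remain. The article does not say whether 5.0 is the SD of change or of a single measurement. It is taken first as the SD of change. Rho is not in the article and is assumed over 0.3 to 0.9, with equal variance s² at both visits. Power is from the noncentral t distribution; no degree of freedom is deducted for the covariate.

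**3. Formulas.**
- Unadjusted change: variance 2s²(1−rho)
- Adjusted for own baseline: variance s²(1−rho²)
- Ratio of adjusted to unadjusted: (1+rho)/2
- Adjusted SD when the SD of change is 5.0: 5.0 × √((1+rho)/2)

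**4. Results, 5.0 as the SD of change, 24 per arm.**

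| Assumed rho | Variance ratio | Adjusted SD | Power, unadjusted change | Power, own baseline added |
|---|---|---|---|---|
| 0.3 | 0.65 | 4.03 | 77% | 92% |
| 0.5 | 0.75 | 4.33 | 77% | 88% |
| 0.7 | 0.85 | 4.61 | 77% | 83% |
| 0.9 | 0.95 | 4.87 | 77% | 79% |

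**5. If 5.0 is the SD of a single measurement.** Unadjusted change has SD 5.0 × √(2(1−rho)) and the adjusted analysis 5.0 × √(1−rho²). Power goes from 60% to 81% at rho 0.3, from 77% to 88% at 0.5 and from 94% to 97% at 0.7. At 0.9 both exceed 99%. The adjusted analysis is never the less precise, apart from the degree of freedom it spends.

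**6. The pooled reading, for completeness.** Suppose the test were a main effect averaged over weeks 0 and 24. The expected difference halves to 4.4/2 = 2.2, and the variance is s²(1+rho)/2. Power at rho 0.3, 0.5, 0.7 and 0.9 is then 47%, 30%, 16% and 6% if 5.0 is the SD of change. If 5.0 is the SD of a single measurement, it falls from 34% at rho 0.3 to 24% at rho 0.9.

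**The case against.** The strongest reply is that nothing here is invalid. The sentence before the model defines the outcome as change, and in an ANCOVA of change with one randomised factor the main effect simply is the treatment contrast. That analysis is unbiased under randomisation and keeps its type I error. The planned sample size never relied on a baseline covariate, so on that reading its omission does not push power below plan: the 77% instead of 80% comes from dropout to 24 per arm and from using the t distribution. The gain also depends on an unknown rho and is small when rho is high. All of this stands.

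A reader might infer from the mention of both weeks and a main effect that the two visits are pooled, which would take power below 50%. The article does not support that as its plan. It never says that the visits are averaged, and it describes repeated-measures models separately, with a treatment-by-time interaction. The low figures are conditional on that reading, on rho and on what the SD of 5.0 refers to.

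Some companion points carry no weight. Tukey's procedure with two arms is redundant and harmless. Calling the randomised factor diet, when both arms receive the same dietary programme, is a naming slip. Whether the glucose-tolerance model includes a visit term is detail that an article may leave to the analysis plan.

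What the reply does not remove is that the article lists its covariates and states its contrast. The list omits own baseline, and the contrast does not match the outcome definition.

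**Conclusion.** The point holds as a matter of efficiency and clarity, and should be fixed. On the natural change-score reading the primary test is valid, but gives up between 35% (rho 0.3) and 5% (rho 0.9) of the residual variance. For MRI that is a power of 77% where about 92% to 79% was available. These figures assume 24 per arm, 5.0 as the SD of change, equal variances at the two visits and the stated range of rho. It does not follow that the primary analysis is biased, or that it is powered below 50%.

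**What to change.** For each primary measure, state one model: the week-24 value (or the change) on treatment, the same measure's baseline value, and the stratification factors sex, age and BMI as fixed terms rather than candidates to be tested. Name the single treatment coefficient, with its confidence interval, as the primary test and estimate. Delete the week-0 comparison and the Tukey step. If a measure is skewed, log both the baseline and the week-24 values; a change score can be zero or negative and cannot be logged directly. Use the same model for secondary outcomes measured at weeks 0 and 24.

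The cost is a reworded paragraph, settled before unblinding, one degree of freedom per model for the baseline term, and a few more for the fixed stratification factors. No new data are needed.
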